# Implementation and Evaluation of a Home-Based Pre-Exposure Prophylaxis Monitoring Option: Protocol for a Randomized Controlled Trial

**DOI:** 10.2196/56587

**Published:** 2024-09-23

**Keywords:** pre-exposure prophylaxis, self-collection, telehealth, sexually transmitted infections, implementation, evaluation, HIV prevention, HIV, PrEP, home-based pre-exposure prophylaxis, HB-PrEP, stigma, home option testing, sexual health, impact, gender, sexual minorities, race, human immunodeficiency virus, United States, sexual minority men, SMM, barriers, barrier, clinical monitoring, monitoring

## Abstract

**Background:**

HIV prevention is a public health priority. Despite progress in recent years, pre-exposure prophylaxis (PrEP) use remains suboptimal especially among groups disproportionately impacted by new HIV diagnoses such as gender and sexual minorities of color. Multiple barriers including a lack of PrEP providers and challenges with attending quarterly monitoring visits contribute to low PrEP uptake and retention. Home-based PrEP (HB-PrEP) services could reduce stigma, increase convenience, expand health system capacity for PrEP care, and improve PrEP retention.

**Objective:**

Home Option Testing for PrEP (HOT4PrEP) is a hybrid randomized controlled trial (RCT) that aims to examine whether HB-PrEP care is acceptable to PrEP users, feasible to implement in a sexual health clinic setting, and impacts PrEP retention.

**Methods:**

The RCT will recruit 458 persons currently taking or soon to initiate PrEP at a sexual health clinic in Seattle, Washington, and randomize them to continue the standard of care or have the option to use HB-PrEP for 2 of 3 triannual PrEP follow-up visits. Participants in the intervention arm will be sent home kits containing gonorrhea and chlamydia swabs and Tasso devices for blood self-collection. The primary outcome is PrEP retention between groups at 20 months; secondary outcomes include user satisfaction and acceptability, feasibility, self-reported PrEP adherence, and sexually transmitted infection (STI) incidence. Interviews with PrEP users and clinic staff will elucidate barriers and facilitators of implementation.

**Results:**

The HOT4PrEP RCT began enrolling in March 2022, was on hold during the height of the US mpox epidemic, then resumed enrollment in December 2022. Of the first 100 enrollees, the median age is 34 years, and most are cisgender gay men (89/100, 89%) with at least some college education (91/100, 91%). Among the 49 participants randomized to the HB-PrEP option, 33 (67%) chose to self-collect samples at home at least once, of whom 27 (82%) successfully returned test kits for HIV and STI testing. Primary PrEP retention and qualitative analyses are ongoing.

**Conclusions:**

Implementation of HB-PrEP into a high-volume sexual health clinic seems to be feasible and acceptable to early RCT enrollees. This strategy has the potential to address individual and systemic barriers associated with initiating and persisting on PrEP, such as increasing sexual health agency and expanding clinical capacity to serve greater numbers of PrEP users.

**Trial Registration:**

ClinicalTrials.gov NCT05856942; https://clinicaltrials.gov/study/NCT05856942

**International Registered Report Identifier (IRRID):**

DERR1-10.2196/56587

## Introduction

### Background

In 2021, the majority of new HIV infections in the United States occurred in sexual minority men [1]. The US federal government targeted resources toward the goal of reducing new HIV infections by 75% by the year 2025 through the “Ending the HIV Epidemic” initiative [2] and highlights the prevention of new infections as a key component of the plan. While pre-exposure prophylaxis (PrEP) has been proven to reduce new HIV diagnoses at the population level [3,4], it remains an underused intervention. Preliminary evidence suggests that only 36% of people in the United States with an indication for PrEP received a prescription in 2022, up only slightly from 30% in 2021 [5]. Though PrEP coverage among sexual minority men at greatest risk for HIV in Seattle-King County, Washington approached 65% in 2021 [6], PrEP use remains low among younger people and some sexual minority men of color [4,6]. As part of its Ending the HIV Epidemic initiative, Public Health-Seattle and King County (PHSKC) aims to achieve ≥70% PrEP coverage among sexual minority men and transgender persons, with equal use among all racial and ethnic groups.

Structural barriers such as lack of access to PrEP medical providers and the burden of quarterly clinical monitoring visits have stymied PrEP scale-up in the United States for years [7-9]. PrEP retention (defined as maintaining all aspects of PrEP care, including attending follow-up visits and obtaining monitoring tests every 3 months according to US guidelines [10]) represents a substantial gap in the PrEP care continuum [11,12]. Studies on national PrEP retention rates suggest only 56% of individuals who initiate PrEP remain on PrEP for at least 1 year, and only 41% persist through year 2 [13]. Younger age, Black race, and unstable or lower income are each associated with discontinuations and being lost to follow-up [14]. We have observed similar levels of PrEP retention in the PHSKC Sexual Health Clinic (SHC), with 40% of PrEP users discontinuing the intervention at least once within 12 months [15]. The COVID-19 pandemic created dramatic reductions in sexual health service capacity [16] that only further exacerbated and continues to impact existing structural barriers that lead to lower PrEP access and higher numbers of discontinuations [17-19]. Among sexual minority men newly diagnosed with HIV in King County, previous PrEP use and discontinuations are common and underscore the urgent need to develop and implement novel targeted strategies to minimize barriers and provide individuals with more options to stay on PrEP [20].

Home-based PrEP (HB-PrEP), whereby an individual self-collects PrEP monitoring specimens at home, mails them into a laboratory for testing, and follows up with a provider remotely to renew PrEP prescriptions, has the potential to decrease PrEP access barriers and increase PrEP continuation rates. Studies confirm that patients are comfortable self-collecting bacterial sexually transmitted infection (STI) screening specimens [21] and that HB-PrEP monitoring is acceptable and often preferable to in-person care [11,22,23]. Configuring PrEP programs to users’ needs can optimize both uptake and delivery [24]. Particularly for young sexual minority men, programs that are convenient, discreet, and provide them with agency over PrEP use and monitoring may reduce the stigma associated with PrEP use, and increase PrEP uptake and retention [11,23]. Furthermore, HB-PrEP may decongest high-volume clinical sites and create additional capacity to grow PrEP programs.

Several direct-to-consumer companies [25] and fewer research or clinic-based PrEP programs provide PrEP services completely from home [22,23,26]. However, opportunities to adequately screen for newly acquired syphilis and HIV in the home setting are often limited. Given that STI incidence is high among people on PrEP, [27] the US Centers for Disease Control and Prevention guidelines recommend PrEP users be screened for STI quarterly, specifically for syphilis and HIV using assays with narrow windows from infection to test positivity [12]. Syphilis is highly associated with HIV acquisition in PrEP users; [28] thus, it is important that PrEP monitoring include tests that can distinguish new from old syphilis, such as with the quantitative rapid plasma reagin (RPR). Approximately 40% of PHSKC PrEP users have a history of syphilis, of which 25% are serofast (have a persistently positive RPR despite treatment in the past) and require a quantitative RPR for syphilis screening [29]. Although previous HB-PrEP studies used procedures that allowed PrEP users to collect all specimens (gonorrhea and chlamydia [GC and CT] swabs and blood samples) from home [22,26], nearly all require fingerstick specimens to perform a less accurate rapid HIV antibody test and collected insufficient blood volume to perform RPR titers, limiting the ability to determine whether titers were stable or indicative of newly acquired syphilis. We previously conducted a pilot study [29] that showed the acceptability and feasibility of using a novel blood self-collection device (formerly Tasso OnDemand, second-generation larger volume device Tasso+) [30] to obtain samples suitable for HIV antigen and antibody and quantitative RPR testing. However, whether these devices could be used successfully within a dedicated program for serial PrEP monitoring remains unknown.

### Objectives

Through a hybrid [31] randomized controlled trial (RCT), we aim to simultaneously evaluate the effectiveness of HB-PrEP as a strategy for improving PrEP retention and its implementation into an urban SHC’s existing PrEP program.

The specific aims of our study are to: (1) evaluate the impact of HB-PrEP on PrEP retention rates among groups assigned to either home-based monitoring or routine care and (2) assess the program’s reach and define the factors that influence HB-PrEP implementation.

## Methods

### Study Overview

The HOT4PrEP (Home Option Testing for PrEP) project is a series of interrelated studies designed to implement and evaluate an HB-PrEP monitoring system that includes the option for biological specimen self-collection at home and remote clinical follow-up in Seattle-King County, Washington. A detailed description of Tasso device use and results of preimplementation acceptability and feasibility analyses are published elsewhere [29]. The current phase of the HOT4PrEP project is an explanatory sequential mixed methods study consisting of 2 components, that are (1) a hybrid RCT wherein we evaluate HB-PrEP as an implementation strategy and its effect on PrEP retention over time along with other secondary outcomes, and (2) semistructured interviews with study participants and clinic staff to explore individual and system-level barriers and facilitators to HB-PrEP implementation.

For the first study component, we will enroll 458 participants from the PHSKC SHC and randomly assign participants 1:1 to either continue the PrEP standard of care ([SOC], control group) or to have an HB-PrEP monitoring option (intervention). Participants in both arms will complete serial web-based surveys and receive PrEP follow-up through telehealth or at the clinic (Textbox 1). At the time of trial conception, monitoring intervals were initially set at every 3 months; however, these changed to every 4 months in March 2023 following the SHC PrEP program’s shift to reduce the total number of required annual visits. HB-PrEP participants receive mailed sampling kits containing instructions and materials to collect extragenital (pharyngeal and rectal) GC and CT swabs and 2 devices to self-collect capillary blood from the upper arm into microtainer tubes. Participants mail kits through United Parcel Service to the PHSKC laboratory for creatinine, quantitative syphilis serologies, and fourth-generation HIV antigen/antibody testing. Secondary outcomes include reach (number of kits requested and used per participant), user satisfaction with the assigned PrEP monitoring program, STI incidence, and time from resulting of abnormal laboratory values to participant notification. Participation in this first RCT component is not incentivized.

For the second component of the study, we will use quantitative data from surveys to inform semistructured interview guides. In-depth interviews will take place with study participants, staff, and administrative personnel to determine factors associated with the program’s implementation.

Study procedures for the home option testing for pre-exposure prophylaxis randomized controlled trial.The home option testing for pre-exposure prophylaxis trial is a hybrid implementation study that randomizes new or current HIV pre-exposure prophylaxis (PrEP) patients at the Sexual Health Clinic in Seattle, Washington, to have the option of home-based monitoring with self-collection of samples for HIV, syphilis, gonorrhea, chlamydia, and creatinine and telehealth follow-up vs standard care including in-clinic visits and monitoring. Trial enrollment began in March 2022 and the primary outcome is pre-exposure prophylaxis retention at 20 months.
**Baseline visit (in-person visit required)**
Intervention arm: Home-based pre-exposure prophylaxis (HB-PrEP) participantsComplete informed consent and enrollment.Confirm baseline laboratory tests are complete (hepatitis A total b, hepatitis B sAb and sAg).Ensure interval monitoring laboratory tests are collected (HIV Ag and Ab enzyme immunoassay (EIA), serum creatinine, quantitative vs quantitative rapid plasma reagin (RPR) based on history of previous syphilis).Participant completes web-based survey.Provide 30-day PrEP supply with 3 refills.Perform home kit teaching.Standard of care (SOC) arm: Routine care participantsComplete informed consent, enrollment.Confirm baseline laboratory tests are complete (hepatitis A total b, hepatitis B sAb and sAg).Ensure interval monitoring laboratory tests are collected (HIV Ag and Ab EIA, serum creatinine, quantitative versus quantitative RPR based on history of previous syphilis).Participant completes web-based survey.Provide 30-day PrEP supply with 3 refills.
**2-4 days later**
Review laboratory results: if HIV or HBsAg is positive, bring the participant to the sexual health clinic for clinical evaluation.
**Month 4, 8, and 16 visits**
Intervention arm: HB-PrEP participants (Follow-up by telehealth)Study staff (PrEP disease research intervention specialist or other trained staff)Assess adherence.Confirm no symptoms of acute HIV or contact with sexually transmitted infection (STI).
Routine PrEP counseling.Order applicable PrEP laboratory tests (HIV Ag and Ab EIA, RPR qual or quant, gonorrhea and chlamydia [GC and CT], creatinine).
Troubleshoot home kit issues.Reminder to return kit with self-collected samples.Reminder to complete web-based survey.Provide 30-day PrEP supply with 3 refills.Schedule or give reminder for next visit.SOC arm: Routine care participantsStudy staff (PrEP disease and intervention specialists [DRISs] or other trained staff)Confirm no signs or symptoms of acute HIV and STI or known sexual contact with a person diagnosed with an STI.If STI contact or concern for acute HIV and STI: notify the clinician, principal investigator (PI), and research coordinator and arrange an in-person evaluation.Draw blood; participant self-collects GC and CT specimens at exposed sites (pharyngeal, vaginal, and rectal).Order and process specimens for HIV Ag and Ab EIA, GC/CT, RPR qual or quant, creatinine (month 6 only).
Provide 30-day PrEP supply with 3 refills.Participant completes web-based survey.Schedule or give reminder for next visit.
**Month 12 visit (in-person visit required)**
PrEP DRISConfirm no signs or symptoms of acute HIV and STI or known sexual contact to a person diagnosed with an STI.If STI contact or concern for acute HIV and STI - notify clinician, PI and research coordinator and arrange in-person evaluation.Draw blood; participant self-collects GC and CT specimens at exposed sites (pharyngeal, vaginal and rectal).Order & process specimens for HIV Ag and Ab EIA, GC and CT, RPR qual or quant, creatinine (may defer if already done within last 3 months).Provide 30-day PrEP supply with 3 refills.Participant completes web-based survey.Schedule or give reminder for next visit.For HB-PrEP or intervention arm enrollees: Troubleshoot home kit issues, provide kit for next visit if desired.ClinicianAssess adherence, side effects, willingness to continue PrEP.Address any participant concerns about PrEP. If issues are related to the study, refer to the research coordinator or PI directly.Complete hepatitis A or B or other vaccines (eg, HPV) if indicated.Provide 30-day PrEP supply with 3 refills.
**Month 20 study exit visit (in-person visit required)**
PrEP DRISConfirm no signs or symptoms of acute HIV and STI or known sexual contact with a person diagnosed with an STI.If STI contact or concern for acute HIV or STI: notify the clinician, PI, and research coordinator and arrange an in-person evaluation.Draw blood; participant self-collects GC and CT specimens at exposed sites (pharyngeal, vaginal, and rectal).Order and process specimens for HIV Ag and Ab EIA, GC and CT, RPR qual or quant, creatinine (may defer if already done within previous 4 months).Provide 30-day PrEP supply with 3 refills.Exit assessment: participant will either complete web-based exit survey or may be selected to participate in exit interview with the research coordinator or PI.

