##### Surveys

Participants in both arms are asked to complete web-based surveys using REDCap (Research Electronic Data Capture) [34]—a secure, web-based platform that participants used successfully in the preimplementation pilot study. The initial enrollment survey collects basic demographic and contact information including valid mailing address and phone number for the participant and an approved alternative contact, sexual orientation and gender identity items, and PrEP monitoring preferences. Subsequent interval surveys focus on evaluating self-reported PrEP adherence, number of sex partners, type and frequency of sex, frequency of drug or condom use, and measures of satisfaction with the assigned monitoring program.

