##### Secondary Outcome Measures

Reach is defined as the proportion of individuals assigned to the HB-PrEP study arm who choose to send in self-collected specimens from home for at least half of tri-annual PrEP visits over the study period. As we are interested in the real-world uptake of HB-PrEP, we are tracking and will report the total number of PrEP patients approached about the study, the number who declined participation and reasons for declination, and the proportion of individuals assigned to the intervention arm who choose at any time to transition to the SOC arm and reasons for doing so. To mitigate potential sampling (self-selection) bias, we explain in the screening process that even if randomized to the intervention arm, the use of HB-PrEP is optional, and patients in the intervention arm can always continue with standard in-clinic monitoring for some or all of the PrEP follow-up visits.

Acceptability or patient satisfaction with HB-PrEP will be evaluated using tri-annual web-based participant surveys including 5-point Likert scale questions adapted from questionnaires of similar PrEP trials. Additional items will inquire about the ease or difficulty of self-sampling device use, issues with receiving kits, and any other challenges with the home monitoring process. Specific validated psychometric tools to assess PrEP user satisfaction are limited overall and, to our knowledge, none exist that are designed to evaluate HB-PrEP services.

Study surveys inquire about PrEP use strategy (event-driven or “2-1-1” vs daily) over the preceding 4 months and adherence questions are tailored to the reported use strategy. Based on data that taking ≥4 doses/week confers a 96% reduction in HIV risk [38], self-reported PrEP adherence is measured using validated question items asking the percent of PrEP taken in the previous 4 weeks [39]. The percentage of PrEP adherence will be compared between arms and analyzed using linear mixed models to account for repeated measures on each participant.

We will measure the time from receipt of monitoring and STI results into the SHC electronic health record to the time study staff notify the participant of abnormal results.

We will also track new syphilis and GC or CT infections for each group per tri-annual interval to estimate a composite asymptomatic STI positivity incident rate.

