##### Qualitative Data

Semistructured interviews will be conducted with HB-PrEP participants (n=24) beginning at month 4 and occur at triannual intervals thereafter, until recruitment goals are reached. The focus of these HB-PrEP participant interviews will be understanding specific barriers and facilitators of PrEP retention, identifying unanticipated negative effects or issues with the delivery of the intervention, determining whether HB-PrEP is preferred to SOC, and how future iterations of the program might be improved. Interview guides will be adjusted based on preliminary data from patient surveys to further explore any issues HB-PrEP participants identify. Clinic staff, including DRIS and administrators (n=3), will also be invited to participate in semistructured interviews at 12 and 20 months to understand operational barriers and facilitators of program implementation. Study participants and staff will be offered their choice of an in-person or virtual interview. Interviews will be audio recorded; transcripts will be independently reviewed by 2 study staff members and evaluated using thematic coding and a mix of inductive and deductive coding.

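### The month-20 exit survey and exit interview are worded as alternatives, so a participant selected for interview may leave without completing the survey

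*Protocol article*

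**What the plan says.** Textbox 1, under the month-20 study exit visit, describes the exit assessment in one sentence: the "participant will either complete web-based exit survey or may be selected to participate in exit interview with the research coordinator or PI". The sentence covers both arms.

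The earlier visits in Textbox 1 differ. At months 4, 8 and 16 the standard-of-care arm completes the web survey and the HB-PrEP arm is reminded to complete it. At month 12 both arms complete it. None of these visits offers an interview as an alternative.

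On the surveys, the Surveys section states: "Participants in both arms are asked to complete web-based surveys using REDCap". On content it adds: "Subsequent interval surveys focus on evaluating self-reported PrEP adherence, number of sex partners, type and frequency of sex", and it goes on to list drug and condom use and satisfaction with the assigned programme. Under Secondary Outcome Measures, satisfaction is assessed through the surveys done three times a year, and for adherence the plan is: "The percentage of PrEP adherence will be compared between arms and analyzed using linear mixed models to account for repeated measures on each participant".

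On the interviews, the Qualitative Data section states: "Semistructured interviews will be conducted with HB-PrEP participants (n=24) beginning at month 4 and occur at triannual intervals thereafter, until recruitment goals are reached". The Study Overview describes the same component more broadly, as "semistructured interviews with study participants and clinic staff to explore individual and system-level barriers and facilitators to HB-PrEP implementation", without naming an arm.

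**The concern.** The survey and the interview do different jobs. The survey yields a percentage-adherence item and Likert satisfaction items. The interview is semistructured and coded for themes, and nothing in the article says that it collects those items. If one replaces the other, an interviewee has no month-20 value on these measures.

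The last visit is the only one with this rule, and it coincides with the end of follow-up. Because the only sized set of participant interviews lies in the HB-PrEP arm, following the rule literally could make survey collection at the final visit differ between arms for a reason that the trial itself creates. An analysis plan cannot recover a survey that was never given.

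**Working it through.** The article gives no figure for exit-survey loss, so there is none to reproduce. The possible loss can be bounded from its other figures.

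**Inputs**
- Arm size: 229 per arm (Sample Size and Power Considerations).
- Expected HB-PrEP retention at 20 months: 68% (same section).
- Participant interviews: 24, all HB-PrEP, from month 4 and every four months until the goal is reached (Qualitative Data).
- Possible interview occasions up to exit: months 4, 8, 12, 16 and 20, that is five.

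**Step 1. Expected HB-PrEP participants still retained at exit.** 0.68 × 229 = 155.7, about 156. Using this as the number who attend the exit visit is an approximation.

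**Step 2. Loss of exit surveys in the HB-PrEP arm, if interviewees skip the survey and exit interviews are among the 24**

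| Timing of the 24 interviews | Falling at month 20 | Share of 229 | Share of about 156 retained |
|---|---|---|---|
| Goal met before month 20 | 0 | 0% | 0% |
| Spread evenly over five visits (assumption) | 24/5 = 4.8, about 5 | 4.8/229 = 2.1% | 4.8/155.7 = 3.1% |
| All at month 20 (upper bound) | 24 | 24/229 = 10.5% | 24/155.7 = 15.4% |

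Under the same conditions the standard-of-care arm loses none, because no interviews of its participants are specified.

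**Step 3. What this could do to a month-20 mean.** Shift in the arm mean = fraction missing × difference between missing and observed participants. The article gives no such difference, so take 10 percentage points of adherence purely as an illustration:
- upper bound, whole arm: 0.105 × 10 = about 1.0 point;
- upper bound, those retained: 0.154 × 10 = about 1.5 points;
- even spread, those retained: 0.031 × 10 = about 0.3 points;
- goal met earlier: 0.

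**Step 4. Which outcomes are exposed.** Retention is defined by completed tests, visits and a renewed prescription (Primary Outcome Measures). It does not use the survey, so the primary outcome and the sample size are unaffected. Adherence and satisfaction do use it.

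**The case against.** A reader might infer something stronger: that month-20 adherence and satisfaction data go missing in the HB-PrEP arm by design, among unusually engaged participants, and so not at random. The documents do not support that, for these reasons.

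- **Arm.** The exit text is not arm-specific. That the exit interview is one of the 24 HB-PrEP interviews is an inference from reading two sections together. Elsewhere the article speaks of interviewing study participants generally. If standard-of-care participants are also selected, the loss is not confined to one arm. If exit interviews are separate from the 24, that number does not bound the loss.
- **Size.** The 10.5% figure needs every interview to fall at month 20. Interviews start at month 4 and stop at the goal, and the Discussion says recruitment for the qualitative component was already under way.
- **Mechanism.** No selection rule for interviewees is given. Selection could be random or could depend on earlier survey answers, which a mixed model can accommodate. Everyone at an exit visit has stayed in follow-up, so engagement does not set interviewees apart.
- **Analysis.** No stand-alone month-20 comparison of adherence or satisfaction is specified. The adherence model uses repeated measures, so an interviewee still contributes earlier surveys.
- **Wording.** The sentence is loose and does not expressly waive the survey. The exit survey's content is not itemised, and a condensed article may leave the order of exit procedures to the full protocol.

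All of this limits the size of the point and removes any claim of demonstrated bias. It does not remove the ambiguity. The sentence is a stated data-collection rule, not an omitted detail, and staff following it could reasonably skip the survey for an interviewee.

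**Conclusion.** The point holds as a minor one. Taken at its word, the exit rule gives up month-20 survey data from participants selected for interview, with no stated reason, on measures for which the survey is the named source. On the only sized interview plan, the loss would probably fall in the HB-PrEP arm. It ranges from 0, through about 5 people (2% of the arm), to at most 24 of 229 (10.5%).

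These figures rest on three assumptions: the literal either/or reading, exit interviews being drawn from the 24, and, for the middle value, even spacing over five visits. The effect is confined to secondary outcomes. For adherence it is softened by the earlier surveys in the mixed model; for satisfaction the article names no model. Whether any missing surveys would be informative cannot be judged without a selection rule.

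**What to change.** Reword the exit assessment in Textbox 1 to state that all participants in both arms complete the web-based exit survey at month 20, before any interview, and that those selected are interviewed in addition. Putting the survey first also keeps the interview from influencing the survey answers. In the same edit, say whether exit interviews count toward the 24 and whether standard-of-care participants can be selected.

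With this change the planned loss of exit surveys falls to 0 of 229, whenever the interviews take place. The cost is a few words of text and a few minutes' extra burden per interviewee. Enrollment was still open when the article was published, so later exit visits can benefit.
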